#### 5.4. Concomitant therapies

Cardiovascular risk factors, including hypertension, dyslipidemia, and diabetes mellitus will be controlled according to generally recommended guidelines using any type of drug. There are no restrictions for physical therapy or diet therapy.

Blood pressure should preferably be controlled with a target systolic blood pressure of  $\leq 130$  mmHg in order to inhibit intracranial hemorrhage.

##### Prohibited concomitant medications

Concomitant use of antiplatelet and anticoagulant drugs other than the study drugs is prohibited.

##### Antiplatelet drugs

Sarpogrelate hydrochloride, dipyridamole, beraprost sodium, limaprost alfadex, alprostadiol, ozagrel sodium, ticlopidine, prasugrel, and combined drugs containing aspirin or clopidogrel

##### Anticoagulants

Warfarin potassium, dabigatran, edoxaban, rivaroxaban, apixaban, heparin products (except for topical external preparation), low-molecular-weight heparin, danaparoid sodium, argatroban, urinastatin, gabexate mesilate, nafamostat mesilate, antithrombin III (freeze-dried concentrated), and human activated protein C (freeze-dried concentrated)

##### Concomitant medications requiring caution

Caution must be exercised when the following drugs are used concomitantly. For details, refer to the insert information of each product.

##### A) Aspirin group

Gout drugs, diabetes mellitus drugs, methotrexate, lithium products, thiazide diuretics, furosemide, azosemide, piretanide, nonsteroidal anti-inflammatory analgesics, ibuprofen, oxicam anti-inflammatory analgesics, alminoprofen, nitroglycerin products, tetracycline antibiotics, new quinolone antibacterials, adrenocortical hormone drugs, sodium lactate, sodium valproate, phenytoin, acetazolamide, angiotensin converting enzyme inhibitors, and  $\beta$ -blockers

##### B) Clopidogrel group

Nonsteroidal anti-inflammatory analgesics and thrombolytic drugs

Drug-metabolizing enzyme (CYP2C19) inhibitors: omeprazole etc.

C) DAPT group only

Drug-metabolizing enzyme (CYP3A4) inhibitors: macrolide antibiotics, HIV protease inhibitors, azole antifungals, cimetidine, diltiazem, grapefruit juice, etc.

Drug-metabolizing enzyme (CYP2C19) inhibitors: omeprazole etc.

## 6. Study Procedures

### 6.1. Observations/tests and observation schedule

Subject observation will follow the schedule below. Timing of each observation is based on the first visit.

| Evaluation item \ Time point                 | (Date of onset) | Enroll-ment | Start of obser-vation | Month 1   | Month 3 | Month 6 | Month 12 | Every 6 months there-after | End of obser-Vation (*) |
|----------------------------------------------|-----------------|-------------|-----------------------|-----------|---------|---------|----------|----------------------------|-------------------------|
| Informed consent                             | ← ○             |             |                       |           |         |         |          |                            |                         |
| Enrollment                                   |                 | ○           |                       |           |         |         |          |                            |                         |
| Observation status                           |                 |             |                       | ○         | ○       | ○       | ○        | ○                          | ○                       |
| Patient characteristics                      | ← ○             |             |                       |           |         |         |          |                            |                         |
| Degree of independence in daily living (mRS) |                 |             | ○                     | ○         | ○       | ○       | ○        | ○                          | ○                       |
| Study drug administration/ compliance        |                 |             | ○                     | ○         | ○       | ○       | ○        | ○                          | ○                       |
| Drugs other than study drug                  |                 |             | ○                     | ○         | ○       | ○       | ○        | ○                          | ○                       |
| Blood pressure                               |                 |             | ○                     | ○         | ○       | ○       | ○        | ○                          | ○                       |
| Head MRI                                     | ← ○             |             |                       |           |         |         |          |                            |                         |
| Head MRI (T2* WI)                            | ← △ →           |             |                       |           |         |         |          |                            |                         |
| Head MRA                                     | ← △ →           |             |                       |           |         |         |          |                            |                         |
| Carotid artery imaging                       | ← △ →           |             |                       |           |         |         |          |                            |                         |
| Laboratory test (blood)                      | ← ○ →           |             |                       | ← ..... → |         |         |          |                            |                         |
| Laboratory test (urine)                      | ← ○ →           |             |                       | ← ..... → |         |         |          |                            |                         |
| Chest x-ray                                  | ← ○ →           |             |                       | ← ..... → |         |         |          |                            |                         |
| ECG                                          | ← ○ →           |             |                       | ← ..... → |         |         |          |                            |                         |
| Adverse events                               |                 |             | ← ..... →             |           |         |         |          |                            |                         |

○ Required item △ Optional item <.....> As required

\* Observation is complete when a subject meets criteria for discontinuation/completion, or when 1 year has elapsed from initiation of observation for last subject enrolled.

### 6.2. Observation days

#### 6.2.1. First day of observation

The first day of observation is the first visit made by an enrolled subject after allocation, and shall take place within 30 days of the enrollment date.

The first day of observation for subjects in the SAPT group is the day when tests etc. described in 6.3.1. *First day of observation* are complete.

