#### 3.2. Inclusion criteria

Patients meeting all of the following criteria will be included:

- 1) Patients with a diagnosis of noncardioembolic ischemic stroke that developed between 8 and 180 days before the first day of observation
- 2) Patients with a responsible lesion identified by head MRI
- 3) Patients 20 to 85 years of age when providing informed consent
- 4) Patients taking aspirin or clopidogrel alone as antiplatelet therapy when providing informed consent
- 5) Patients meeting at least one of the following criteria:
  - i. At least 50% stenosis of a major intracranial artery (to the level of A2, M2, P2)
  - ii. At least 50% stenosis of an extracranial artery\*
 

\* common carotid artery, internal carotid artery, vertebral artery, brachiocephalic artery, or subclavian artery
  - iii. Two or more of the following risk factors:
    - 65 years of age or older
    - Diabetes mellitus
    - Hypertension
    - Peripheral arterial disease
    - Chronic kidney disease
    - History of symptomatic ischemic stroke (excluding the index IS for this study)
    - History of ischemic heart disease
    - Smoking (only current smokers, excluding previous smokers)
- 6) Patients able to visit the study center throughout the observation period

7) Patients who provided written informed consent for participation

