## 11. Statistical Analysis

### 11.1. Rationale for target sample size

We assumed an annual recurrence rate of 4% in the monotherapy group based on data from the EVEREST study and the aspirin monotherapy group in the JASAP study. We also assumed a 30% decrease in relative recurrence risk (in other words, an annual relapse rate of 2.8%) in the DAPT group with cilostazol. The number of subjects required was calculated at 1,688 per group using the methods described by Lakatos et al in our main analytical method of the log-rank test (conditions were assumed relapse rates for each group, a 2.5 year enrollment period, a maximum 3.5 year observation period,  $\alpha=0.05$ , and a statistical power of 80%). This results in a total target sample size of 4,000 (2,000 per group), assuming an annual dropout rate of 5% during the study period.

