##### **ITT analysis set**

The ITT analysis set is defined as the population of all randomized subjects. The subjects in this set belong to one of the treatment groups to which subjects were randomized, regardless of the drug they were actually administered.

The analysis set will be reexamined before database lock.

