## **9. EFFICACY EVALUATION**

### **9.1 Primary endpoint**

The first recurrence of ischemic stroke between the first and last observation days (during the observation period) will be included in the analysis.

Subjects discontinued for reasons other than occurrence of the primary endpoint and subjects who continue to study completion will be treated as censored subjects. The censor date will be considered the observation completion date.

- 1) A between-groups comparison for the period from the observation start date to the date of ischemic stroke recurrence will be performed using the log-rank test, and the superiority of the combination therapy group versus the monotherapy group will be examined.
- 2) Survival coefficients for the period from the observation start date to the date of ischemic stroke recurrence will be estimated for each treatment group using the Kaplan-Meier method and plotted.
- 3) The hazard ratio for ischemic stroke recurrence in the combination therapy group versus the monotherapy group and its 95% confidence interval will be determined using a Cox proportional hazard model.
- 4) An adjusted hazard ratio will be calculated using a Cox proportional hazard model that includes as covariates age (each 1 year), sex, ischemic stroke clinical subtype (atheromic, lacunar, other, unknown), mRS (ordered categorical data).
- 5) The annual incidence in each group will be calculated using the person-year and Kaplan-Meier methods. The 95% confidence interval of the incidence will be calculated using the approximate Poisson method and the Greenwood method. One year will be considered 365.25 days for the calculations.

- 6) A subgroup analysis will be performed for each variable shown in Table 6.8 using a Cox proportional hazard model that includes a comparison group and predictive factors. The hazard ratio for the combination therapy group versus the monotherapy group will be calculated for each stratification category based on the predictive factors. Uniformity will be examined for the stratification categories based on the interaction between the comparison group and predictive factors.
- 7) Frequency distributions for each treatment group will be determined for the findings regarding the clinical subtype of ischemic stroke (lacunar, atherothrombotic, other, unknown) and responsible lesion (supratentorial, infratentorial, both, unknown) at the time of ischemic stroke onset.

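### Efficacy and safety clocks start at a visit up to 30 days after an open randomisation, so early events go uncounted and subjects with no first visit have no start date

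*Supplement*

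**What the plan says.** Protocol v1.3, section 4.1, has the investigator enrol the subject through the internet system and then read the allocated group from it. The arm is therefore known from enrolment.

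Section 6.2.1 places the start of observation later: "The first day of observation is the first visit made by an enrolled subject after allocation, and shall take place within 30 days" of the enrolment date. A second sentence applies to one arm only: "The first day of observation for subjects in the SAPT group is the day when tests etc" listed in 6.3.1 are complete. Under 5.1.2, cilostazol begins on the first day of observation.

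SAP 9.1 limits the primary endpoint to that window: "The first recurrence of ischemic stroke between the first and last observation days (during the observation period) will be included in the analysis". It runs the log-rank comparison from the observation start date. SAP 9.2 (secondary endpoints) and 10.1 (adverse events) use the same window, and SAP 6.2.4 and 6.2.5 measure person-time and time to event from the same day.

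SAP section 5 says: "The ITT analysis set is defined as the population of all randomized subjects". SAP 6.4 rules out imputation. Neither document says what happens to a randomised subject who has an event, dies or withdraws before the first visit.

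Inclusion criterion 1 (protocol 3.2) is tied to the same later date: "noncardioembolic ischemic stroke that developed between 8 and 180 days before the first day of observation".

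**The concern.** Randomisation protects a comparison that starts at randomisation. Here it starts at a later visit, in a trial where investigators know the arm in the meantime. If that knowledge changes who attends or how soon, the groups compared at time zero are no longer simply the randomised groups. This is post-randomisation selection.

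Three things follow.

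- Events in the gap fall outside every efficacy and safety analysis and may not be collected systematically. The first-day list in protocol 6.3.1 has no item on events since enrolment; event status first appears among the later observations in 6.3.2. Immediate SAE reporting in 23.2.1 is framed mainly around the observation period.
- A subject with no first visit belongs to the ITT set but has no time-to-event value.
- The SAPT-only rule allows the start day to be set differently in the two arms. It is also unclear whether the 30-day limit covers the day the SAPT tests are completed.

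The rationale for criterion 1 in protocol 3.2 says that recurrence becomes less frequent with time since the stroke. The uncounted days therefore come early, when risk is higher.

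The direction of any bias is not fixed. Leaving out cilostazol-free DAPT time moves the estimate towards benefit compared with a strict from-randomisation effect. A later SAPT start under a falling hazard would work against DAPT.

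**Working it through.** **Inputs.** Protocol 11.1: "We assumed an annual recurrence rate of 4% in the monotherapy group"; for DAPT, "in other words, an annual relapse rate of 2.8"% (hazard ratio 0.70); "a 2.5 year enrollment period, a maximum 3.5 year observation period"; 80% power, two-sided 5%; 2,000 per group; 5% annual dropout. Rates are used as constant hazards and enrolment as uniform. The gap length and the early rate are not in the documents; both are assumptions below.

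**1. The plan's own figure.** Events needed (Schoenfeld): 4 × (1.960 + 0.842)² / (ln 0.70)² = 246.8, so 247. With follow-up of 1.0 to 3.5 years, the event probability at hazard h is P(h) = 1 − [e^(−h) − e^(−3.5h)] / (2.5h). This gives P(0.04) = 0.0857 and P(0.028) = 0.0609, sum 0.1466. Then 246.8 / 0.1466 ≈ 1,684 per group, against the stated 1,688. A numerical Lakatos calculation gave 1,715. The sample size reproduces and is not at fault.

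**2. Events counted from the first visit.** With 2,000 per group and dropout hazard −ln(0.95) = 0.0513, expected events are 161 + 114 = 276. Power: z = (√275.6 / 2) × 0.3567 − 1.960 = 1.00, or 84.2%.

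**3. Strokes in the gap.** Cilostazol has not started, so both arms take the monotherapy rate λ. For a gap of g days in every subject, uncounted strokes = 4,000 × (1 − e^(−λg/365.25)).

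**4. Effect of counting them.** Gap strokes carry a hazard ratio of 1. Averaging the log hazard ratio over events, with y gap strokes: average HR = exp[ln 0.70 × 275.6 / (275.6 + y)]. Power then follows as in step 2 with 275.6 + y events.

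| Gap, every subject | Rate | Uncounted strokes | Share of all events | Average HR | Power |
|---|---|---|---|---|---|
| 10 days | 4%/yr | 4.4 | 1.6% | 0.704 | about 83.6% |
| 30 days | 4%/yr | 13.1 | 4.5% | 0.711 | about 82.5% |
| 10 days | 8%/yr (assumed) | 8.8 | 3.1% | 0.708 | about 83.0% |
| 30 days | 8%/yr (assumed) | 26.2 | 8.7% | 0.722 | about 80.8% |

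The 30-day rows are an upper end, because they put every subject at the limit. Protocol v1.3 section 10.2 extends enrolment to March 2017. With 3.5 years of enrolment, about 328 events are expected from the first visit, and 13.1 gap strokes would be 13.1 / 341.3 = 3.8% of the total.

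**The case against.** The strongest defence is that neither arm takes cilostazol in the gap and both continue the same background drug, so gap events should balance apart from attendance effects. Starting the clock at treatment start also keeps untreated days out of the comparison. This stands as far as it goes. It explains why the average effect is small, but it does not exclude arm-dependent attendance or supply a rule for subjects without a first visit.

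A reader might infer several stronger points that the documents do not support.

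- *Immortal-time bias.* Events and person-time both start on the observation start date in both arms (SAP 6.2.4, 6.2.5, 9.1). No event-free time is credited to either arm.
- *Start dates that always differ by arm.* Protocol 6.3.1 accepts test results from stroke onset onwards and applies to both arms. The SAPT tests may already be complete at the first visit, so the dates can coincide.
- *Patients becoming ineligible and being removed after randomisation.* The scheduled first-visit date and the eligibility confirmation are entered at enrolment (protocol 4.1), so the 180-day limit can be checked in advance. If a visit then slips, the ITT definition keeps the subject.
- *A stated exclusion of those who never return.* The ITT set includes them. What is missing is a rule for analysing them.
- *A shortfall against the 247 events.* The plan counts its follow-up in observation time, so the uncounted strokes are additional to the planned information.

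**Conclusion.** The concern holds in this form: primary, secondary and safety events are counted from a visit that can fall up to 30 days after an open allocation. Events before it are omitted, and randomised subjects without it have no start date, which does not fit the ITT definition. The SAPT-only rule allows, but does not force, different start days.

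At the planning rate the size is modest: about 4 to 13 uncounted strokes for assumed gaps of 10 to 30 days, an average hazard ratio of at most about 0.71 in place of 0.70, and up to about 2 points of power. An assumed early rate of 8% per year raises the count to about 9 to 26. These figures assume the same gap for every subject and equal risk in both arms before the first visit. They do not measure bias from arm-dependent attendance. The documents give no evidence on whether that would occur, and its net direction is unknown. This should be fixed.

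**What to change.** - In SAP 6.2.4, 6.2.5, 9.1 and 9.2, time the primary and secondary endpoints from the randomisation date in both arms and count all events from that date.
- Add a CRF item at the first visit for events since enrolment. That item cannot reach subjects who never attend; for them, use any event or vital-status information the site holds and censor at the last known date, or at the randomisation date if there is none.
- Reconcile the two sentences of protocol 6.2.1 into one start-of-observation rule for both arms.
- Keep the observation-start analysis as a sensitivity analysis.
- In SAP 10.1, report adverse events both from randomisation and from the first observation day, so that cilostazol-free days do not dilute the bleeding comparison.
- State that a first visit slipping past day 180 does not remove a randomised subject.

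Cost: SAP wording, one CRF item, some site follow-up for non-attenders and a short amendment. Allocation is made through the enrolment system, so the randomisation date should already be on record. The downside is that a few cilostazol-free days in the DAPT arm slightly dilute the effect and cost up to about 2 points of power at the planning rate, from about 84% to 82.5%.

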#### 6.2.2. At 1, 3, 6, and 12 months

Subjects will be observed at 1, 3, 6, and 12 months (determined days) following the first day of observation.

#### 6.2.3. From 12 months onward

Subjects will be observed every 6 months.

**6.2.4. Acceptable variation of days of observation**

Acceptable variations in days of observation are as follows.

|                                        |                               |
|----------------------------------------|-------------------------------|
| Month 1                                | ± 2 weeks from determined day |
| Month 3                                | ± 4 weeks from determined day |
| Month 6                                | ± 8 weeks from determined day |
| Month 12 and every 6 months thereafter | ± 8 weeks from determined day |

**6.2.5. Completion of observation**

Observation will be completed for all subjects at 1 year after observation begins or the last subject enrolled in the study.

**6.3. Observation, test, and report items****6.3.1. First day of observation**

The following items, including patient background, will be observed. All test data from day of onset to first day of observation will be used.

- Date of first visit
- Age and sex
- Height (cm)
- Weight (kg)
- Date of most recent noncardioembolic ischemic stroke
- Medical history and complications
  - Coronary artery disease: No or Yes
  - Peripheral arterial disease: No or Yes
  - Hypertension: No or Yes
  - Diabetes mellitus: No or Yes
  - Dyslipidemia: No or Yes
  - Chronic kidney disease: No or Yes
  - History of ischemic stroke (excluding the index ischemic stroke for this study): No or Yes
- Smoking habit: No (nonsmokers or previous smokers) or Yes (current smokers of ≥1 cigarette/day)
- Modified Rankin Scale (mRS) (see 29.5 *Modified Rankin Scale*)
- Statuses of study drug treatment
  - Drug name, prescription start date, and dosage and administration
- Drugs used other than study drugs
- Blood pressure
- Head MRI (required)

Date of scan (between stroke and enrollment)  
 Clinical subtype: lacunar, atherothrombotic, or other  
 Responsible lesion: supratentorial, infratentorial, or both

- Head MRI T2\* (optional)
  - Date of scan (between stroke and enrollment)
  - Microbleeds: No or Yes, (location and number)
- Head MRA (optional)
  - Date of scan (between stroke and enrollment)
  - At least 50% stenosis of a major intracranial artery (to the level of A2, M2, or P2):  
No or Yes
- Image evaluation of cervical arteries (optional)
  - Laboratory procedures: CTA, MRA, ultrasound, DSA
  - Date of scan (between stroke and first observation)
  - At least 50% stenosis of an extracranial artery (the common carotid artery, internal carotid artery, vertebral artery, brachiocephalic artery, or subclavian artery): No or Yes
- Clinical laboratory tests
  - Hematology: white blood cell count, red blood cell count, hemoglobin, hematocrit, and platelet count
  - Clinical chemistry: AST, ALT, TC, TG, HDL-C, creatinine, fasting blood glucose, uric acid, and HbA1c (only for patients with diabetes mellitus)
  - Urinalysis: Glucose, protein, and occult blood
- Chest X-rays Normal/Abnormal
- ECG Normal/Abnormal

